### Describing the Cost of the Intervention

Specific Aim #3 is "Calculate the cost of the intervention." Describing the costs associated with the mouth care intervention and developing methods for documenting these costs are important for evaluating the public health impact of the intervention and provides the basis for future, more elaborate cost analysis work. Because this is a new intervention with little data describing its cost, activity-based costing methods will be used to determine the cost of the intervention prospectively. Costs that will be determined will include developmental and training costs, costs associated with identifying and enrolling participants, overhead, equipment and supply costs, and personnel expenses. Intervention costs will be dichotomized as being either fixed or variable: fixed costs do not vary with the number of patients treated and include the costs of office space, administrative support and equipment (such as computers or cell phones); variable costs do vary with the quantity of services provided and include personnel costs (time spent by caregivers in providing services) and supplies. For personnel costs, time spent by each staff member on activities related to the intervention will be tracked using activity logs, which will be checked regularly for accuracy. Total time spent on the intervention will then be multiplied by the hourly wage, including fringe benefits, to determine costs of personnel time. Intervention costs will include the costs of training the interventionists, but will exclude costs associated with research and monitoring, such as costs of training the CRB raters, time spent by CRB raters, and costs related to the randomization of study subjects.

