## Methods/Design

A randomized repeated measures design will be used in this clinical trial. NH residents will be randomized at the individual level to the experimental group, which will receive the intervention, or to the control group, which will receive standard mouth care from research team members who receive training in the proper methods for providing mouth care but no training in resistance recognition or resistance prevention/mediation. For baseline data collection, the behavior raters (research assistants trained to observe and record CRB) will observe both control and experimental NH residents receiving mouth care from the NH staff twice daily (AM: after breakfast but before lunch and PM: immediately after the evening meal) for 7 days. Members of the experimental and control groups will then receive mouth care from interventionists (research team members trained to provide mouth care) twice daily for 21 days, using the same schedule. A 21-day intervention period provides the greatest opportunity for obtaining the maximum benefit from the MOUTh intervention. Oral health outcome data will be collected 5 times: once prior to the 7-day observation period; once after the 7-day observation period but before the initiation of the intervention; after 7 days of intervention; after 14 days of intervention; and after 21 days of intervention. This schedule, which is depicted in Table 1 is designed to fully capture changes in oral health throughout the progression of the study.

**Table 1 T1:** Intervention & Data Collection Schedule

	Steps & Measures	Frequency
Recruitment	**Screen and Consent** Written consent from responsible party Examination of medical records to confirm inclusion/exclusion criteria Examination of NH resident for ability to hold toothbrush, raise hand to mouth MMSE Resnick et al.'s Evaluation to Sign Consent if MMSE 18 or higher Written consent from NH resident if 6/8 questions answered correctly on Resnick et al.'s Evaluation to Sign Consent	Once

Baseline, pre-observation	**Randomization (Experimental or Control) and Baseline** Baseline Chart Review (demographic data, co-morbidities) Global Deterioration Scale (GDS) Katz Activities of Daily Living (ADL) Oral Health Assessment Tool (OHAT)	Once Once Once

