### Description of the MOUTh Intervention

The MOUTh intervention was developed and pilot-tested in a previous study[35]. It contains three components: best mouth care practices for older adults with natural dentition and dentures[36-40]; recognition of CRB[16,41]; and strategies to reduce threat perception during the provision of mouth care[35,36,40,42-44]. The mouth care protocol integrates best mouth care practices with threat reduction strategies derived from the neurobiological, nursing, and dental literature. For example, best mouth care practices included using warm water for rinsing and using interdentate brushes for flossing[36-40]. Threat reduction strategies are a constellation of techniques congruent with previously cited neurobiological and nursing studies. These techniques, which were culled from extant literature as well as from techniques that were successfully employed in a previously published pilot study[35], include interventionist behaviors designed to minimize threat appraisal, such as smiling and relaxed demeanor,[45] distraction, bridging (having an elder hold a toothbrush while the interventionist brushes the elder's teeth), and cueing (the use of polite, one-step commands)[40,42]. Interventionists are trained to encourage the elder to do as much of his or her mouth care as possible. The rationale for this technique is that self-care is unlikely to be perceived as threatening[45]. Experimental interventionists are also trained to avoid the use of "elderspeak," a term used to describe "baby talk" speech patterns associated with infants and pets but inappropriately employed when engaged with older adults: high pitch, short sentences, sing-song cadence, patronizing tone, use of collective pronouns, and infantilizing terms (baby, honey, dearie)[43,44]. Elderspeak is a documented trigger to CRB[43,44] because its dehumanizing approach heightens threat perception.

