Describing the costs associated with the MOUTh intervention and developing methods for documenting these costs is important for evaluating the public health impact of the intervention. Because this is a new intervention with little data describing its cost, activity-based costing methods will be used. Determining the cost of the intervention will involve several steps. First, resources used to deliver the intervention will be determined.. These resources will include personnel, supplies and other expenses. Next, the amounts used of these resources will be documented. In the case of personnel time, the amount of time spent on activities related to the intervention will be determined using data from the RTC-r instrument, in which the exact amount of time (in seconds) the interventionists required to perform mouth care will be recorded. The amounts used of each resource will be multiplied by the unit cost of each resource to determine the cost associated with the resource. For personnel costs, the time spent by each experimental interventionist will be multiplied by the hourly compensation associated with CNAs. Finally, costs will be summed across all components of the intervention and divided by the number of NH residents treated to determine the average cost per NH resident of delivering the MOUTh intervention. These data will inform a future cost-effectiveness study.

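### The two cost passages for Aim 3 do not agree on whether trial enrolment enters the average cost per resident, and if it is kept in, that average is biased upward

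*Protocol article*

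**What the plan says.** Calculating the cost of MOUTh is the third of the primary specific aims (protocol article, Background). Two sections describe how.

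*Describing the Cost of the Intervention* says that activity-based costing will establish the cost of the intervention prospectively. It then lists the costs to be determined: "developmental and training costs, costs associated with identifying and enrolling participants, overhead, equipment and supply costs, and personnel expenses". Later in the same paragraph, interventionist training is counted in, whereas the intervention cost "will exclude costs associated with research and monitoring, such as costs of training the CRB raters, time spent by CRB raters". Randomization is a further exclusion named there: "costs related to the randomization of study subjects". Personnel time comes from staff activity logs and is priced at the hourly wage with fringe benefits.

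*Statistical Analysis* starts from what is used to deliver the intervention: "These resources will include personnel, supplies and other expenses". Personnel time comes from the session times on the RTC-r form. The time of the experimental interventionists is priced at CNA compensation. The sum over components is "divided by the number of NH residents treated to determine the average cost per NH resident of delivering the MOUTh intervention". These data are to feed a later cost-effectiveness study.

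**The concern.** The first section names enrolment on its cost list and names randomization as an excluded research cost. In this trial the two are the same kind of work. Table 1 describes recruitment as "Written consent from responsible party Examination of medical records to confirm inclusion/exclusion criteria", followed by a check of toothbrush handling, the MMSE and, where the score allows, a capacity-to-consent evaluation. The Instruments and Measures section says that the MMSE serves to determine capacity for consent. Most of this would not be done by a nursing home that simply adopted MOUTh.

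Two analysts could each follow the text and report different average costs. One would keep enrolment because it is a named item. The other would drop it as research, or because the Statistical Analysis section never mentions it. The first figure would overstate the cost of delivery, and the overstatement would pass into the planned cost-effectiveness work.

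**Working it through.** **1. The two sections side by side**

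| Element | Describing the Cost of the Intervention | Statistical Analysis (cost paragraph) |
|---|---|---|
| Components | Development, training, identification and enrolment, overhead, equipment and supplies, personnel; research and monitoring excluded | Personnel, supplies, other expenses used in delivery |
| Enrolment | Named on the list; not named among the exclusions | Not named |
| Source of personnel time | Activity logs | RTC-r session times |
| Rate | Hourly wage with fringe benefits | CNA hourly compensation |
| Divisor | Not stated | Residents treated |

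**2. Does the Statistical Analysis section settle the matter?** RTC-r session times contain no enrolment time, so on a literal reading enrolment labour adds 0%. But they contain no training time either, and the other section expressly includes interventionist training. Session time therefore cannot be the whole personnel numerator if both sections are to hold. Enrolment could still enter through the activity logs or through other expenses.

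**3. Direction.** Let E be the enrolment cost booked to the intervention and T the number of residents treated. Keeping enrolment in adds exactly E/T to the average, so the bias can only be upward.

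**4. Size.** The document gives no cost, wage, enrolment time or session length, so there is no cost figure to reproduce. The headcounts do check: 60 / (1 − 0.25) = 80 recruited, 40 per group, as stated in Recruitment, Sample, Sample Size.

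Inputs from the document: 42 planned sessions per resident and T = 40. Inputs assumed: h = 0.5 to 2 staff-hours per enrolment, m = 3 to 10 minutes per session, one wage for all hours, and only the 40 experimental-arm enrolments booked.

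Added share = (h × 40/40) / (42 × m/60)

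Delivery hours per resident: 42 × 3/60 = 2.1; 42 × 5/60 = 3.5; 42 × 10/60 = 7.0.

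| Hours per enrolment | 3 min (2.1 h) | 5 min (3.5 h) | 10 min (7.0 h) |
|---|---|---|---|
| 0.5 | 24% | 14% | 7% |
| 1 | 48% | 29% | 14% |
| 2 | 95% | 57% | 29% |

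The extremes are 0.5/7.0 = 7% and 2/2.1 = 95%. These are shares of direct mouth care hours, not of total cost. Supplies, training and overhead in the base would lower the percentages; a higher wage for enrolment staff than for delivery would raise them.

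**The case against.** The strongest reply is that the plan already excludes enrolment. The list is of costs to be determined, which can be read more widely than intervention costs, and the research exclusion is introduced by an open-ended set of examples. If consent and capacity testing are research, that exclusion removes them, and the Statistical Analysis calculation would not pick up their labour anyway. This stands to the extent that a reader may not infer that the protocol counts enrolment as an intervention cost, or that the average *is* inflated. It does not remove the inconsistency. The list follows directly on the sentence about determining the cost of the intervention, the paragraph names no other total that the list could feed, and excluding enrolment means overriding a named item.

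Four further inferences are tempting and are not supported:

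- **Two enrolments charged per treated resident.** Dividing 80 enrolled by 40 treated gives 2 and doubles the range to 14% to 190%. The arithmetic is right, but no text books control-arm enrolment to MOUTh, and the Statistical Analysis section prices experimental interventionists only.
- **Past development costs spread over the trial's residents.** The article says "The MOUTh intervention was developed and pilot-tested in a previous study", but costs are to be determined prospectively and nothing says that earlier spending is recovered.
- **Training and overhead should leave the average.** The plan openly includes them. That is a choice of costing perspective, and it already separates fixed from variable costs.
- **All identification work is research.** Finding residents who resist mouth care may be needed in routine use. The point is limited to consent, capacity testing and trial-eligibility work.

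It is also fair to say that a condensed article leaves costing detail to the full protocol. But this is a conflict in what the article states, not an absent detail.

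**Conclusion.** The point holds as an inconsistency to be reconciled. The two sections give different numerators for the Aim 3 average, and they differ on time source and wage. If enrolment is kept in, the average cost of delivering MOUTh is biased upward by trial consent, capacity-testing and eligibility work. The 7% to 95% range is an illustration that rests wholly on the assumed times and on booking experimental-arm enrolments alone; the document itself does not fix the size. Aim 3 is descriptive and carries no hypothesis, so the tests of H1 and H2 are untouched. Severity is low.

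**What to change.** 1. In Describing the Cost of the Intervention, state that consent, capacity testing and trial-eligibility and enrolment work are research costs, excluded from the intervention cost alongside randomization. Identification of suitable residents that routine use would need may stay, shown as its own line.
2. Align that section with Statistical Analysis on one component list, one time source and one wage, applied to the experimental arm. If session times are used for delivery, say where training time is taken from.
3. Keep interventionist training and overhead as the plan chooses, and show the fixed and variable parts of the average separately.

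The cost is a rewording of two paragraphs. No new data are needed provided the activity logs distinguish enrolment from delivery and training; the article does not say whether they do, so this should be confirmed before the logs are used. If enrolment would otherwise have been counted, the reported average will be lower.

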### Procedures

Table 1 (at the end of the manuscript) illustrates the steps in the proposed study along with the data collection schedule.

### Statistical Analysis

Individual growth models using multilevel analysis will be used to estimate the efficacy of the intervention for reducing CRBs in persons with dementia, and to estimate the overall efficacy of the intervention using oral health outcomes. Multilevel models (also referred to as hierarchical linear models) will be used because repeated observations of participants are nested within nursing homes[48,64-68]. Multilevel models deal with the "unit of analysis" problem that face nested studies, that is the units of analysis are not independent, but instead the observations are clustered[48,66,69,70]. Because multiple observations are nested

within participants (i.e., repeated measures), individual growth models will be used. Among the advantages of using individual growth models are the ability to deal with an unequal number of measurement occasions among individuals and heterogeneity of variance[48,65,66,71].

Three-level multilevel models will be estimated for CRBs and oral health outcomes in which the first level is the date/time at which the behaviors or outcomes are observed; the second level is the participant; and the third level is the NH in which the participant resides. Explanatory variables to be included at the first level are dosage; frequency; time; and a dummy variable for baseline versus intervention. Explanatory variables to be included at the second level are a dummy variable for whether the participant is in the intervention group or control group; functional status; cognitive impairment; demographic data (gender, ethnicity, race, age, duration of stay in a nursing home); co-morbid conditions; and the use of psychoactive medications. Variables are discussed and defined above.

Describing the costs associated with the MOUTh intervention and developing methods for documenting these costs is important for evaluating the public health impact of the intervention. Because this is a new intervention with little data describing its cost, activity-based costing methods will be used. Determining the cost of the intervention will involve several steps. First, resources used to deliver the intervention will be determined.. These resources will include personnel, supplies and other expenses. Next, the amounts used of these resources will be documented. In the case of personnel time, the amount of time spent on activities related to the intervention will be determined using data from the RTC-r instrument, in which the exact amount of time (in seconds) the interventionists required to perform mouth care will be recorded. The amounts used of each resource will be multiplied by the unit cost of each resource to determine the cost associated with the resource. For personnel costs, the time spent by each experimental interventionist will be multiplied by the hourly compensation associated with CNAs. Finally, costs will be summed across all components of the intervention and divided by the number of NH residents treated to determine the average cost per NH resident of delivering the MOUTh intervention. These data will inform a future cost-effectiveness study.

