***Cognitive impairment ***is a co-variate to CRBs because CRB increases exponentially as cognitive impairment progresses[60]. This variable will be operationalized as a score of 2 or greater on the **Global Deterioration Scale (GDS)**. This instrument is used to quantify dementia severity by placing it in one of seven stages: (1) no cognitive decline-normal, 2) very mild cognitive decline-forgetfulness, (3) mild cognitive decline-early confusional, (4) moderate cognitive decline-late confusional, (5) moderately severe decline-early dementia, (6) severe cognitive decline-middle dementia, and (7) very severe cognitive decline-late dementia[61]. Other researchers have noted correlations from 0.88 - 0.91, P < .05 over six data collections with the Alzheimer's Disease Assessment Scale (ADAS)[62]. The data from the GDS will be used to identify relationships between the severity of cognitive decline and CRBs. The **Mini-Mental State Examination, MMSE**[49] will be used to determine capacity for consent and will be obtained once, during the consent process.

***Demographic data, co-morbidities***, and ***use of psychoactive medication ***are control variables that will be collected from the medical records at baseline. *Demographic data *are necessary for comparisons between control and experimental subjects. Co-morbidities will be collected using the *Charlson Co-morbidity Index*,[63] a weighted index that takes into account the number and seriousness of co-morbid diseases, to calculate a co-morbidity score for each subject. *Use of psychoactive medication *will be calculated from the medical records. Actual received dosages of regularly scheduled and "as needed" anti-depressant medication and anti-psychotic medication will be summed for each subject daily for the 7-day observation period and the 21-day intervention period. Both co-morbid diseases and psychoactive medication use may explain fluctuations in CRBs during the study.

***New infections***. Medical records will also be examined weekly for any new diagnosis of infection (e.g., urinary tract infection, pneumonia), and such infections will be recorded as bivariate data. This variable is a mediating variable for CRB. The "new infection" variable will be used as a control variable for RTC-r scores.

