***Time ***is an independent variable that will be incorporated into statistical models to determine the effect of the intervention on CRB and oral health status over specified temporal intervals and shifts (day and evening).

***Dosage ***and ***frequency ***of the intervention are independent variables that will be incorporated into statistical models to determine the effect of the intervention on CRB and oral health status, and to compare the efficacy of the intervention to standard mouth care. Dosage will be calculated by the observer, using a stopwatch to measure the duration of each mouth care session. Dosage is also used to calculate the rate of care-resistance using the RTC-r. Frequency will be measured by counting the number of times mouth care was completed; percentage of completed mouth care will be calculated for each NH subject by dividing the number of successful mouth care completions by 42 (twice daily mouth care for 3 weeks).

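### The efficacy models adjust for session duration and completed sessions, which arise after randomisation, so the treatment coefficient is not the total randomised effect that H1 and H2 ask for

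*Protocol article*

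**What the plan says.** All references are to the protocol article.

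- **Purpose of the model.** Statistical Analysis: "Individual growth models using multilevel analysis will be used to estimate the efficacy of the intervention for reducing CRBs in persons with dementia". The same models serve the oral health outcomes.
- **Level 1.** "Explanatory variables to be included at the first level are dosage; frequency; time; and a dummy variable for baseline versus intervention".
- **Level 2.** "a dummy variable for whether the participant is in the intervention group or control group; functional status; cognitive impairment", then demographics, and "co-morbid conditions; and the use of psychoactive medications".
- **Role of dosage and frequency.** Instruments and Measures says that these two features "of the intervention are independent variables that will be incorporated into statistical models to determine the effect of the intervention on CRB". It says the same for oral health, and that they serve the efficacy comparison with standard mouth care. Treatment Fidelity treats the same two quantities as measures of receipt of the intervention.
- **Definitions.** Dosage is the stopwatch duration of the session. Frequency is a count of completed sessions; a percentage per resident with denominator 42 is also defined. For duration the text adds: "Dosage is also used to calculate the rate of care-resistance using the RTC-r".
- **Psychoactive medication.** Instruments and Measures places it among the control variables taken from the records at baseline, then says that received amounts "will be summed for each subject daily for the 7-day observation period and the 21-day intervention period".
- **New infections.** The same section calls this a mediating variable for CRB and then says that it "variable will be used as a control variable for RTC-r scores". It does not appear in the Statistical Analysis covariate list.

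The article describes no efficacy model without dosage and frequency.

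**The concern.** H1 and H2 (end of Background) compare MOUTh with usual mouth care. In a trial randomised by resident, that contrast is protected only as long as the model conditions on nothing that assignment can change. Dosage and frequency fail this test.

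**Frequency.** Description of Usual Care notes that residents who resist often get no mouth care at all. Completion therefore depends on resistance, which is the H1 target. Instruments and Measures names resistance as a mediator for H2, and the Abstract says that oral health deteriorates without daily hygiene. The protocol's own chain is MOUTh, less resistance, more completed care, better oral health. Holding completions fixed in the H2 model blocks the last part of that chain.

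**Dosage.** MOUTh adds distraction, bridging, cueing and encouraged self-care, any of which could lengthen or shorten a session. Resistance could do the same. Duration also divides the CRB count to form the rate, so in the H1 model it stands on both sides of the equation. Because the outcome is already standardised by duration, entering duration again is not a plain exposure adjustment.

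At stake is what the two main efficacy estimates mean: a direct-type effect that is open to bias from unmeasured causes shared by the covariate and the outcome, not the total effect of allocation.

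**Working it through.** **1. What the plan's own figure shows.** The plan gives no figure for this bias. The one relevant number is the denominator of the completion percentage: 2 sessions × 21 days = 42. The 2 × 7 = 14 baseline sessions are not in it, so the percentage is wholly an intervention-phase quantity.

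**2. Timing.** Table 1 puts randomisation before the 7-day observation phase and the 21-day intervention phase. Session duration and completions on days 8 to 28 therefore follow both allocation and the start of allocated care.

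**3. Effect of conditioning (all parameters assumed).** Let g be arm (0/1), M a post-randomisation covariate with within-arm SD 1, and U an unmeasured cause of both M and the outcome Y:

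M = a·g + u_M·U + error; Y = d·g + b·M + u_Y·U + error.

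- Total effect of assignment = d + a·b.
- Slope on M given g = b + u_M·u_Y.
- Adjusted group coefficient = d + a·b − a(b + u_M·u_Y) = d − a·u_M·u_Y.

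Take d = −0.3, b = −0.4, u_M = −0.5 and u_Y = +0.5, so that u_M·u_Y = −0.25. The total is −0.3 − 0.4a and the adjusted coefficient is −0.3 + 0.25a. If treatment has no effect on Y (d = b = 0), the total is 0 and the adjusted coefficient is 0.25a.

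| Shift a in covariate (SD) | Total | Adjusted | Adjusted when true effect is 0 |
|---|---|---|---|
| 0 | −0.30 | −0.30 | 0 |
| 0.25 | −0.40 | −0.2375 | +0.0625 |
| 0.5 | −0.50 | −0.175 | +0.125 |
| 1 | −0.70 | −0.05 | +0.25 |

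Least-squares fits to 400,000 simulated observations agree (for example −0.180 and +0.123 at a = 0.5).

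**4. Duration as denominator and covariate (assumed inputs).** Control sessions have a Poisson CRB count with mean 4 and a log-normal duration with median 4 minutes and log SD 0.4. The mean rate is 4 × exp(0.4²/2)/4 = 1.083 per minute. If MOUTh multiplies the count by c and the duration by k, the difference in mean rate is 1.083 × (c/k − 1). The last column is simulated.

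| c | k | Unadjusted rate difference | Adjusted for duration |
|---|---|---|---|
| 1 | 1.5 | 1.083 × (1/1.5 − 1) = −0.36 | −0.08 |
| 0.7 | 0.7 | 1.083 × (1 − 1) = 0 | −0.32 |
| 0.7 | 1 | 1.083 × (0.7 − 1) = −0.325 | −0.325 |
| 0.7 | 1.5 | 1.083 × (0.7/1.5 − 1) = −0.58 | −0.335 |

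Here duration differs by arm but is not caused by resistance. The adjusted coefficient then roughly tracks the count, while the unadjusted rate does not.

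**5. The same adjustment when resistance lengthens the session.** Assume a session of 3 minutes plus 0.5 minute per CRB, about 30% fewer CRBs with MOUTh, 30 residents per arm and 42 sessions each. In 25 simulated data sets the rate fell 20% without duration in the model and 5% with it, while the count fell 31%. With no within-resident link between duration and resistance, both models gave −28%.

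The adjusted coefficient can therefore be harmless, helpful or badly attenuated, depending on a mechanism that cannot be known in advance.

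**The case against.** **Adjusting for duration can remove an artefact.** In the first row of step 4, CRB counts are equal and MOUTh sessions only last longer. The rate falls by a third (1 − 1/1.5), and the duration term takes most of that away. This stands: a primary model that drops duration but reports only the rate stays sensitive to session length. It is an argument for analysing the count per session beside the rate. It does not rescue the duration term, which fails when resistance itself drives session length (step 5).

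**The article does not say which coefficient is the efficacy estimate.** With group, phase and time in the model, it could be an interaction. True, but a group-by-phase or group-by-time contrast is altered in the same way if assignment shifts duration or completions during the intervention phase.

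**The level of frequency is open.** Both a count and a per-resident percentage are defined, and a running count could properly sit at level 1. This stands, so the level at which frequency is listed is not itself held to be an error.

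**Stronger readings to avoid.** A reader might infer that the intervention is intended to change session length, medication and infections. The aims and hypotheses name only CRB and oral health, and effects on systemic illness are left to long-term objectives. That assignment can affect duration and completions is enough. A reader might also infer that the listed model conditions on new infections and on-study medication. Infections are a control for RTC-r in Instruments and Measures only. For medication the text gives both a baseline and a daily on-study timing, and entry at level 2 fits a baseline value; this is a conflict to reconcile, not proof of post-randomisation adjustment.

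**Conclusion.** The point holds for dosage and frequency, which suffice on their own. The article states that they enter the models used to estimate efficacy and to compare it with standard mouth care; this is not a detail left to an unseen analysis plan. Followed as written, the models do not estimate the total randomised effect for either H1 or H2.

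Size and direction cannot be derived from the document. If assignment does not shift duration or completions, there is no bias. If it does, the assumed examples run from mild to near-complete attenuation (−0.70 to −0.05 at a shift of 1 SD) and include a non-zero coefficient where there is no effect. A reader might take the fall from 20% to 5% in step 5 as an expected loss of three quarters of the effect. It is not: it rests on invented session lengths and few replicates, and how much is lost depends on how far session length varies for reasons other than resistance. Completions, medication and infections were not simulated by name, nor was H2; step 3 covers them only in general form.

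The point should be settled before analysis because it touches both efficacy hypotheses.

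**What to change.** 1. Make primary, for CRB and for oral health, a model with group, time, phase, their interactions, site and pre-intervention covariates only: ADL score, GDS stage, co-morbidity index, demographics, and psychoactive use from the 7-day baseline. That window follows randomisation but precedes the allocated care, since both arms are then still served by nursing home staff. State which coefficient is the efficacy estimate.
2. Move dosage and frequency to secondary mediation or dose-response models, labelled as such.
3. Because the rate depends on session length, analyse CRB count per session, session duration and percentage of sessions completed by arm alongside the rate.
4. Reconcile the two statements in Instruments and Measures on whether psychoactive use is a baseline or an on-study value. Keep any adjustment for on-study medication or new infections out of the primary model.

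Cost: analysis wording and a secondary model. All the variables are already collected. Dropping the two covariates may slightly lower precision.
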